### Data management and processing

#### Data management

Data are submitted to a secure university server. Participants are allocated a unique identification code that is used for all study records to maintain confidentiality and protect their identity. All treatment sessions are audio recorded for fidelity purposes. Audio recordings are labelled by the clinician and saved on the secure server at the end of each session.

#### Power considerations

We have powered the study for Hypothesis 1A. Hypotheses 1A tests the outcome (i.e. adherence) related to what makes PA-CBTI unique from traditional CBTI. Given the relatively small sample size of our pilot PA-CBTI data (unpublished), we have benchmarked our power analysis to find a medium effect (Cohen’s f = 0.25) in a 3 × 5 (group × session) multivariate analysis of variance (MANOVA) (five sessions, as there are no adherence data in weeks 1 or 2). With alpha = 0.05 and a two-tailed test, a sample size of 120 (40 per group) provides a power of 0.81 to detect a significant effect. Follow-up comparisons also have adequate power [55].

#### Statistical tests of hypotheses

##### Aim 1

Hypothesis 1A predicts that individuals under partner-assisted conditions will show greater adherence and lower attrition than those under the individual treatment condition. We will test this with 3 × 5 (group × session) MANOVA. The MANOVA will first test the entire set of adherence variables by constructing a latent variable of adherence and using this as the outcome variable. If significant, we will then examine the univariate results for each specific adherence measure. Significant main effects of group (the hypothesised effect) will be followed by comparing PA-CBTI with each of the other groups. Hypothesis 1B will use the Chi-squared test to test the proportion of participants who complete each treatment, with similar follow-ups.

##### Aim 2

Hypothesis 2A anticipates that greater adherence will relate to better sleep outcomes in PA-CBTI and i-CBTI, but not PA-SMT. Multiple regressions will test the hypothesis, with explanatory variables of group (dummy coded), adherence (in the last week of treatment), and group × adherence interaction. The outcome variable will be diary-derived sleep efficiency in the last week of treatment. The interaction term is the effect of interest. Follow-ups will examine the adherence effect within each group. Hypothesis 2B will be tested with Sobel mediation. We hypothesise that PA-CBTI will show (via sleep diaries) greater mean daily sleep efficiency at post-treatment and 6-month follow-up compared with i-CBTI. This effect will be mediated by adherence at the end of treatment (adherence cannot be measured at follow-up since we will not be prescribing sleep schedules).

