A recent review shows that adherence to CBTI in the clinical settings ranges from 32–52% [21]. The lowest rates were in clinical effectiveness studies and studies with comorbid populations [21]. Not surprisingly, even modest improvements in CBTI adherence can improve outcomes [22]. Findings from a study of 696 clients with insomnia found that those who completed treatment with high adherence improved significantly more than completers with low adherence [22]. Additionally, adherence is the strongest predictor of long-term (e.g. 1 year) outcomes [22]. Attrition also reduces the benefits of treatment, especially in clinical settings where dropout rates are reported to be as high as 39% [23, 24]. A study on the national dissemination of CBTI in the US Veteran Affairs Healthcare System reported that 33% of clients dropped out [24]. Together, these studies suggest a sizable proportion of clients are likely not to be fully benefiting from CBTI. Efforts to broadly implement CBTI would benefit from ways to improve treatment adherence and completion rates. There currently are no evidence-based recommendations for augmenting either treatment adherence or completion in CBTI.

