#### Hypothesis 1B

Participants in the partner-assisted treatment will evidence higher treatment completion rates than i-CBTI.

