### Participants

Study participants (*n* = 120 completers) are clients and their partners recruited from the Monash Healthy Sleep Clinic (Melbourne, Australia) and the community via advertisement, e.g. radio, newspaper, flyer drops, and social media. Our estimated recruitment numbers shown in Fig. 1 are based on a 4:1 referral-to-screening ratio, and our initial screening visit goal assumes a 20% screen failure rate. Our randomisation numbers assume 20% attrition. These rates are similar to those we have experienced in other similar insomnia trials.

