### Study intervention

Following pre-treatment assessments, couples are randomised to one of three interventions: PA-CBTI, i-CBTI, or PA-SMT. All three interventions consist of seven weekly, 1-h sessions. Participants can discontinue the treatment or the study at any stage. If one of the members of the couples wishes to withdraw, they must withdraw as a couple. Post-treatment and 6-month follow-up data will be collected for those who discontinue the treatment unless they withdraw from the study.

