#### Attrition analysis

Analysis of non-completers will be assessed based on those who were scheduled for an initial treatment session. We document the reasons for attrition throughout, and will assess the difference between completers and non-completers, as well as the differential attrition rates between treatment conditions. This forms part of the secondary hypothesis given completion is one of the main outcome variables.

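### The MANOVA chosen for Hypothesis 1A needs all five weekly adherence scores, while the trial itself expects dropout to differ by arm

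*Protocol article*

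**What the plan says.** Under Statistical tests of hypotheses (Aim 1), the protocol article names a 3 × 5 MANOVA for Hypothesis 1A: "The MANOVA will first test the entire set of adherence variables by constructing a latent variable of adherence". A significant group effect leads to comparisons of PA-CBTI with each other arm. The Sleep diaries section places the five adherence measurements at sessions 3 to 7, all after randomisation.

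Power considerations gives the target as "f = 0.25) in a 3 × 5 (group × session) multivariate analysis of variance" and states: "With alpha = 0.05 and a two-tailed test, a sample size of 120 (40 per group) provides a power of 0.81". The Participants section describes the same 120 as "120 completers) are clients and their partners" and inflates the number randomised for 20% attrition, with no difference by arm.

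Hypothesis 1B reads: "Participants in the partner-assisted treatment will evidence higher treatment completion rates than i-CBTI". On dropout in routine care, the Background cites a national dissemination study that "reported that 33% of clients dropped out" and an upper figure of 39%.

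Study intervention puts randomisation after the pre-treatment assessments. It keeps post-treatment and 6-month collection going for people who stop treatment but stay in the study. On attrition the article says: "Analysis of non-completers will be assessed based on those who were scheduled for an initial treatment session". Completion is tested by Chi-squared, and that paragraph gives no denominator.

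**The concern.** A classical repeated-measures MANOVA treats the five session scores as one response vector and omits anyone whose vector is incomplete. Staying to session 7 is a post-randomisation event that the trial expects treatment to change. Restricting the adherence comparison to those who stay then compares a more heavily selected i-CBTI group with a less selected PA-CBTI group. If partners keep weaker adherers in treatment, PA-CBTI would look worse on adherence because it did better on completion. This affects the hypothesis on which the trial was powered.

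The visits kept for people who stop treatment do not repair this, because adherence is scored only at sessions 3–7.

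There is a smaller, related matter. Attrition is counted among couples scheduled for a first session, although allocation comes earlier. A couple lost between the two would fall outside the count.

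**Working it through.** **1. The plan's own power figure.** For a group effect averaged over m = 5 sessions, λ = f²·N·m / (1 + (m − 1)ρ), with 2 and 117 degrees of freedom. With f = 0.25 and N = 120, the numerator is 0.0625 × 120 × 5 = 37.5. The between-session correlation ρ is not given.

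- ρ = 0.5: λ = 37.5/3.0 = 12.5, power 0.89
- ρ = 0.676: λ = 37.5/3.704 = 10.1, power 0.81
- ρ = 0.8: λ = 37.5/4.2 = 8.9, power 0.76

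The stated 0.81 can be matched at ρ of about 0.68 but not verified. In any case 120 enters as the number analysed. Since the Participants section calls these completers, the number randomised is 120/(1 − 0.20) = 150, or 50 per arm.

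**2. The target in SD units.** If both partner arms exceed i-CBTI by the same d, as hypothesised, the SD of the three arm means is d·√2/3 = 0.471d. Setting this to 0.25 gives d = 0.53. The article does not state 0.53; another pattern of means would give another value.

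**3. Bias from analysing those who stay.** Suppose a fraction p leaves and retention correlates r with adherence (normal, SD 1). The mean among stayers then shifts upward by r·φ(z_p)/(1 − p). Inputs are p = 0.33 for i-CBTI (cited in the article), p = 0.15 for PA-CBTI (assumed) and r from 0.3 to 0.7 (assumed).

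- φ(z)/(1 − p) is 0.541 at p = 0.33 and 0.274 at p = 0.15
- r = 0.3: 0.082 − 0.162 = -0.08 SD, or 15% of 0.53
- r = 0.5: 0.137 − 0.270 = -0.13 SD, or 25%
- r = 0.7: 0.192 − 0.378 = -0.19 SD, or 35%

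The sign is PA-CBTI minus i-CBTI. With equal p the two shifts cancel.

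**4. Other assumed dropout pairs.** A simulation used two arms of 50, one adherence score per client and a t-test among stayers. Cells give results for r = 0.3 / 0.5 / 0.7.

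| Dropout i-CBTI v PA-CBTI | Mean difference, no true effect | Rejection rate, no true effect | Power, true 0.5 SD |
|---|---|---|---|
| 20% v 20% | 0.00 / 0.00 / 0.00 | 0.06 / 0.05 / 0.05 | 0.62 / 0.64 / 0.69 |
| 30% v 10% | -0.09 / -0.15 / -0.21 | 0.06 / 0.11 / 0.17 | 0.46 / 0.37 / 0.30 |
| 33% v 10% | -0.10 / -0.17 / -0.24 | 0.07 / 0.12 / 0.20 | 0.41 / 0.31 / 0.21 |
| 39% v 20% | -0.08 / -0.13 / -0.20 | 0.06 / 0.09 / 0.15 | 0.40 / 0.35 / 0.30 |

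This is a simplified single-score comparison, not a re-run of the planned MANOVA.

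**5. Completion denominator.** Study intervention places randomisation before session 1. Attrition analysis counts from scheduling of session 1. Aim 1 of the tests section names neither as the base for the Chi-squared test. Only couples lost between allocation and scheduling are at issue, and the article gives no count of them, overall or by arm. No bias can be calculated.

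**The case against.** The strongest objection is that nobody is expressly excluded. The article names no analysis set and no missing-data rule. Sizing on completers with a 20% allowance is ordinary and does not commit the trial to a completer analysis. A latent-variable fit can retain partial data, and an unseen analysis plan may deal with gaps. All of this stands, so deletion is an inference from the named test. Against it, MANOVA is the stated method, and an analysis plan that kept partial sessions would have to depart from its classical form.

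It is also fair that the 15% and the correlations have no source in the article, that the plan itself assumes one attrition rate, and that unequal dropout is only a hypothesis. Under the assumptions used, the bias runs against the trial's own hypothesis. It mainly threatens the chance of detecting a benefit, not a false claim of PA-CBTI superiority.

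Three stronger readings are tempting, and the document does not support them:

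- **Both primary outcomes lose randomised couples in an arm-dependent way.** For completion this is not shown. The base is couples scheduled, not couples who attended, so those who fail to appear still count as non-completers. The section also commits to recording reasons for attrition and comparing it between arms.
- **The completion count flatters the partner arms.** Early loss could differ in an unblinded trial, but nothing indicates how much or in which direction.
- **The joint-withdrawal rule distorts the primary outcomes.** The rule, "If one of the members of the couples wishes to withdraw, they must withdraw as a couple", does not change who is counted in either primary analysis. Adherence is scored during treatment, and people who only stop treatment are still followed up.

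**Conclusion.** The concern holds for adherence, in a limited form. The named test handles incomplete session data poorly, and the trial's own hypothesis makes unequal losses the expected case. Under 33% v 15% dropout and correlations of 0.3–0.7, the contrast shifts by about -0.08 to -0.19 SD against PA-CBTI. Three conditions carry this result: clients with incomplete sessions are dropped, dropout is higher in i-CBTI, and leavers adhere less. If dropout is equal the bias is zero; if leavers adhere better, the sign reverses.

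For completion, the finding is only that the denominator should be fixed at all randomised couples. No size or direction can be given.

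**What to change.** Replace the MANOVA with a likelihood-based linear mixed model for the session-level adherence outcome, with group, session and group × session. Include every randomised client with at least one session 3–7 score, and use the same model for the individual adherence measures. This suits an article that already describes its trial as mixed-effects.

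The model has limits. It relies on data being missing at random, how much of the shift above it would remove has not been shown, and a client who leaves before session 3 gives it no score. So pre-specify a missing-not-at-random sensitivity analysis that covers those early leavers, for example imputation with a range of arm-specific downward shifts in adherence. Simply scoring later sessions as non-adherent is less suitable, because non-adherence has no natural value on a scale of minutes of deviation.

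State all randomised couples as the denominator for the 1B Chi-squared test and for the attrition analysis.

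The cost is a change of analysis wording, with no new data collection. Completion percentages may come out slightly lower.

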#### Hypothesis 1A

Participants in the partner-assisted treatment will show better treatment adherence to SRT and SC, measured by daily sleep diaries and greater overall adherence on clinician-rated adherence forms, relative to those receiving individual CBTI.

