##### Sleep diaries

Sleep diaries are widely used in studies of insomnia [44]. Each morning, participants are asked to record sleep habits such as bedtime, wake time, time in bed, and number and duration of awakenings and naps. Weekly averages are calculated. Sleep diaries include questions to track treatment adherence. Adherence to sleep restriction is calculated as average nightly deviation, in minutes, between the prescribed bed/wake times and reported times, plus any nap time [41, 45]. Note that, consistent with sleep restriction, clients are not considered “non-adherent” if they go to bed later or wake up and get out of bed earlier than scheduled times as they are taught this will simply increase sleep debt and aid treatment. Stimulus control adherence involves two questions: the first asking how many wake minutes after lights-out were spent out of bed (we then calculate that as a proportion of total wake minutes), and the second asking how many minutes outside the sleep window were spent in bed doing any activity other than sleep. Sleep management therapy adherence is measured by documenting the extent to which the treatment recommendation(s) to be practised each week is followed. Additionally, adherence to sleep restriction and stimulus control will still be calculated, despite these not being treatment recommendations. Hence, this group serves as a control for how much these behaviours change without a specific focus on them. While having several measures of adherence poses analytical challenges, the advantage is it allows us to assess exactly where, if anywhere, adherence fails. Adherence measures are obtained in sessions 3–7 (changes to sleep commence at session 2). We considered also using actigraphy to assess adherence (i.e. objective measure of bed time/wake time in sleep restriction). However, we decided against this, since actigraphy cannot measure stimulus control (i.e. cannot determine whether motion is in or out of bed) or assess sleep hygiene.

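### The three-arm latent adherence test does not protect the measure-level PA-CBTI versus i-CBTI comparisons, because PA-SMT can make it significant on its own

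*Protocol article*

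**What the plan says.** Protocol article, Statistical tests of hypotheses, Aim 1, sets three steps. A 3 × 5 (group × session) MANOVA first tests a latent adherence variable. Next: "If significant, we will then examine the univariate results for each specific adherence measure". Where the group effect is significant, PA-CBTI is compared with each of the other two arms. None of the steps has a multiplicity adjustment or its own alpha.

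The only alpha in the article is in Power considerations: "With alpha = 0.05 and a two-tailed test, a sample size of 120 (40 per group) provides a power of 0.81 to detect a significant effect".

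The measures are primary outcomes, and Hypothesis 1A names them separately. It predicts that partner-assisted participants "will show better treatment adherence to SRT and SC, measured by daily sleep diaries and greater overall adherence on clinician-rated adherence forms". On the simplest count there are four: one sleep restriction deviation and two stimulus control scores (Sleep diaries), and one clinician total (Client adherence form). The Sleep diaries section recognises the difficulty: "While having several measures of adherence poses analytical challenges, the advantage is it allows us to assess exactly where, if anywhere, adherence fails".

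Two further statements matter. The PA-SMT section says that sleep restriction and stimulus control are kept out of that treatment, and that the main purpose of the trial is PA-CBTI against i-CBTI. The Sleep diaries section says that both behaviours are nevertheless scored in PA-SMT, as a control.

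**The concern.** A single overall test followed by unadjusted tests limits false positives only while nothing differs. Once one real difference makes the overall test significant, the later tests run unprotected.

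Here such a difference is built into the design. An arm that is never given a sleep schedule or stimulus control instructions may well score lower on both, whether or not the partner has any effect. That alone can make the latent test, and each univariate three-arm test, significant. PA-CBTI and i-CBTI are then compared on four measures in turn.

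At stake is the component-level message of Aim 1. The trial could report that partners help with, say, stimulus control when PA-CBTI and i-CBTI do not differ on it, and what partners are trained to do could be shaped by that result.

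**Working it through.** **The plan's own figure.** The article states no familywise error rate. Its one figure is power 0.81, for the first-stage test. For a between-group effect averaged over m = 5 sessions, the noncentrality is λ = N f² m / (1 + (m − 1)ρ) = 120 × 0.0625 × 5 / (1 + 4ρ) = 37.5 / (1 + 4ρ), on 2 and 117 df.
- ρ = 0.65: λ = 37.5 / 3.6 = 10.4, power 0.822.
- ρ = 0.70: λ = 37.5 / 3.8 = 9.9, power 0.799.

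So 0.81 fits a between-session correlation of 0.65 to 0.70, which the article does not state. It says nothing about the measure-level tests beyond "Follow-up comparisons also have adequate power".

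**Inputs from the article.** Three arms of 40; alpha 0.05 two-sided; four measures; the three-step order.

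**Assumptions.** Follow-up tests use 0.05, the only alpha given. Measures are session averages, normal and equally correlated, scored so that higher is better. The latent score is the mean of the four. Correlations and PA-SMT shifts are not in the article, so ranges are shown.

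**Benchmark, once the first two steps are passed.** For k independent null tests the chance of any false positive is 1 − 0.95^k.
- k = 3: 1 − 0.857 = 14.3%.
- k = 4: 1 − 0.815 = 18.5%.

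For k = 4 with correlation 0.3, 0.5 and 0.8 it is 17.5%, 15.6% and 11.4%.

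**Whole sequence simulated** (24,000 trials per setting). Step 1: three-arm F on the latent score. Step 2: three-arm F on each measure. Step 3: PA-CBTI versus i-CBTI t test, pooled variance, 117 df. Entries are the chance of at least one false PA-CBTI versus i-CBTI difference, in either direction.

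| True state | ρ = 0 | 0.3 | 0.5 | 0.8 |
|---|---|---|---|---|
| PA-SMT 1 SD lower on all four | 18.7% | 17.3% | 15.6% | 11.0% |
| PA-SMT 0.5 SD lower on all four | 17.8% | 16.3% | 13.9% | 10.3% |
| PA-SMT 1 SD lower on the three diary measures only | 16.5% | 15.6% | 14.0% | 10.4% |
| PA-SMT 1 SD lower, and PA-CBTI truly 0.8 SD higher on the clinician rating (errors on the other three) | 14.4% | 13.4% | 12.3% | 9.9% |
| Only the clinician rating differs (PA-CBTI 0.8 SD higher), PA-SMT not shifted (errors on the other three) | 3.6% | 3.4% | 3.6% | 2.9% |
| No difference anywhere | 1.6% | 2.5% | 2.8% | 2.9% |

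In the first row the latent test is significant in practically every trial. Counting only errors that favour PA-CBTI, that row becomes 9.8%, 8.7%, 7.9% and 5.5%, against 2.5% for a single two-sided test.

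In the fifth row the latent test is significant in only 43.5%, 23.9%, 18.9% and 15.0% of trials, which is why the error stays low.

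**With Holm** over the four PA-CBTI versus i-CBTI contrasts after the latent test, the first row becomes 4.8%, 4.6%, 4.1% and 3.0%.

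**The case against.** The plan does contain a multiplicity rule. One latent outcome is tested first, measures are looked at only if it is significant, and only two of the three pairwise contrasts follow. This is a familiar protected-MANOVA sequence, and the follow-ups can be read as locating an effect already shown. A condensed article may also leave the level of follow-up tests to an analysis plan that is not shown, and it names no alpha for them.

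Part of this stands. Testing the follow-ups at 0.05 is an inference from the one alpha given. If the first stage compared only PA-CBTI with i-CBTI, or if PA-SMT's sleep restriction and stimulus control scores were kept out of it, the route described here would close. But the article does set out its rule: a three-group test, with PA-SMT scored on those behaviours. It also treats the measures as primary. The weakness lies in the stated rule and is not merely an omitted detail.

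Three stronger readings are not supported.
- **That the error is 11–19% whatever the truth.** It depends on PA-SMT differing. If nothing differs, the error is below 3%.
- **That any single real effect exposes the other measures.** With a 0.8 SD difference on the clinician rating alone, the latent test is usually not significant and the error is about 3–4%. Even with both partner arms 1.5 SD higher on one measure it is 6.2% at correlation 0, falling to 3.4% at 0.7.
- **That the primary latent test is itself inflated.** It remains at 0.05.

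**Conclusion.** The point holds in a conditional form. The three-arm latent test gives no strong error control for the measure-level PA-CBTI versus i-CBTI contrasts, because PA-SMT can pass the first two steps alone. If PA-SMT is 1 SD lower and PA-CBTI equals i-CBTI on all four measures, the chance of at least one false difference is about 11–19% for correlations from 0.8 down to 0. At 0.5 SD it is about 10–18%. About half of these errors favour PA-CBTI (roughly 5–10%).

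The sizes rest on an inferred count of four measures, assumed correlations and PA-SMT shifts, and follow-up tests at 0.05. The result does not need an extreme shift, and it survives when PA-SMT is lower on the diary measures only. It should be corrected, but it does not undermine the latent test of Hypothesis 1A.

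**What to change.** In Statistical tests of hypotheses, Aim 1, make one of two changes.

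1. After the latent-score test, define the measure-level family as PA-CBTI versus i-CBTI on the four adherence measures. Test it with Holm at two-sided 0.05. Report the measure-level PA-CBTI versus PA-SMT contrasts descriptively, with intervals.
2. Or label all measure-level results descriptive, and let only the latent-score PA-CBTI versus i-CBTI contrast support Hypothesis 1A.

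Either is about a sentence of wording and needs no new data. The cost of the first is power for individual measures. The smallest of the four p-values must reach 0.05 / 4 = 0.0125. For a 0.5 SD difference with 40 per arm (noncentral t, 78 df, noncentrality 0.5 × √20 = 2.24), power is 0.60 at 0.05 and 0.38 at 0.0125. That is the strictest step; later Holm steps use 0.0167, 0.025 and 0.05. The second option costs the right to make confirmatory claims about single components.

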#### Partner-assisted sleep management therapy (PA-SMT)

Sleep management therapy includes all aspects of CBTI, except sleep restriction therapy and stimulus control: the 3P model of insomnia, sleep hygiene, stress and relaxation, cognitions and sleep, and relapse prevention. We use the 3P model in PA-SMT because it does not include conditioned arousal as the fourth factor, as this factor is intimately tied to stimulus control. While the primary goal of this study is to compare PA-CBTI with i-CBTI regarding adherence and attrition, inclusion of a non-active control arm facilitates interpretation of results. Specifically, PA-SMT will help control for the interaction of non-specific therapy factors and the involvement of the partner. We expect this condition to show high adherence without conferring benefits to sleep. This is also a valuable control because sleep hygiene (the core of SMT) is the only treatment many individuals with insomnia are offered given that CBTI is typically is only available in specialty clinics. If results indicate that adding the partner increases adherence (as expected) and this, in turn, increases sleep outcomes, PA-SMT would be a much more cost effective way of treating sleep problems than i-CBTI or PA-CBTI. To be clear, we do not expect that outcome, but it would be remiss not to examine for it. In PA-SMT, a different topic is covered in each session, including education about sleep-wake cycle, sleep hygiene, exercise, diet, alcohol, and caffeine. Sleep restriction and stimulus control principles are strictly avoided. Prior studies have shown that SMT is a credible and well-accepted intervention, though it does not improve sleep [43, 43].

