### Strengths

Strengths of the current project include the range of outcome variables, which permits high-quality analysis. Our focus on optimising external validity by maximising generalisability to clinical settings and implementing relatively few exclusion criteria is a significant strength, given clinic-based studies and clients with comorbidities show reduced adherence and completion relative to more tightly controlled RCTs. In addition, our control condition, sleep management therapy (PA-SMT), is a valuable control given that it is considered ‘treatment as usual’ in the community. Results could lead to the dissemination of a new CBTI intervention that helps more people adhere to and complete treatment, ultimately benefiting a greater number of people who seek treatment for insomnia. PA-SMT allows us to assess for the unique contribution of the partner independent of the active treatment. Another strength of this trial is our multimodal assessment of sleep; that is, both prospective (e.g. sleep diaries) and retrospective (e.g. ISI) data are collected. Furthermore, we control for clinician time and effort in that clinicians dedicate the same amount of time and effort to each of the three treatment conditions. This trial is also not limited to the investigation of how the interventions impact on sleep since data on broader outcomes will be analysed, including relationship functioning and mental health. Finally, this trial will allow a robust analysis of the impact of insomnia and its treatment on the bed partner, something not examined to date (Additional file 1).

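### The named primary comparison, PA-CBTI versus i-CBTI, is tested only after a significant three-group test, and the stated power of 0.81 belongs to that three-group test

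*Protocol article*

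**What the plan says.** In the Protocol article, the section on partner-assisted sleep management therapy states that "the primary goal of this study is to compare PA-CBTI with i-CBTI regarding adherence and attrition". It describes PA-SMT as a non-active control included to help interpretation.

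Under Statistical tests of hypotheses, Aim 1, Hypothesis 1A is tested with a 3 × 5 (group × session) MANOVA. The pairwise step is conditional: "Significant main effects of group (the hypothesised effect) will be followed by comparing PA-CBTI with each of the other groups". For completion, "Hypothesis 1B will use the Chi-squared test to test the proportion of participants who complete each treatment, with similar follow-ups".

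Power considerations says the study is powered for Hypothesis 1A, which it ties to what distinguishes PA-CBTI from traditional CBTI. The figure is for the 3 × 5 MANOVA at f = 0.25 and two-tailed alpha 0.05: "a sample size of 120 (40 per group) provides a power of 0.81 to detect a significant effect". For the pairwise step it says only that "Follow-up comparisons also have adequate power", with a citation but no difference, alpha or power value.

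**The concern.** The question called primary concerns two arms, but its test can proceed only if a test involving a third arm is significant first. PA-SMT does not prescribe sleep restriction or stimulus control, yet adherence to both is scored in that arm (section Sleep diaries). Its position can therefore raise or dilute the three-group effect for reasons unrelated to the partner.

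Two things follow. A real partner effect can be missed because the three-group test fails. And the quoted 0.81 does not tell the reader how likely the trial is to detect the difference between PA-CBTI and i-CBTI.

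**Working it through.** **Inputs from the document.** 40 per arm (120 in total), f = 0.25, five sessions, two-sided alpha 0.05, power 0.81 (Power considerations); 20% attrition (Participants). **Assumed:** the between-session correlation ρ, which is not stated, and the position of PA-SMT. The model is a group main effect on each client's five-session mean, which simplifies the planned MANOVA.

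**1. The plan's own figure.** λ = N f² × 5/(1 + 4ρ), referred to F(2, 117).
- ρ = 0.5: λ = 120 × 0.0625 × 5/3 = 12.5, power 0.89.
- ρ = 0.676: λ = 7.5 × 5/3.704 = 10.12, power 0.81.
- ρ = 0.8: λ = 7.5 × 5/4.2 = 8.93, power 0.76.

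So 0.81 is reached at ρ of about 0.68. This value was solved for. It shows that 0.81 is attainable, not that it was derived this way.

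**2. What f = 0.25 implies for the pair.** f is the SD of the three group means in units of the within-group SD. Setting it to 0.25:
- PA-SMT equal to PA-CBTI, i-CBTI lower by g: SD of means = g√(2/9), so g = 0.25/0.471 = 0.53.
- PA-SMT midway, PA-CBTI above i-CBTI by h: SD of means = h/√6, so h = 0.25 × 2.449 = 0.61.
- PA-SMT beyond one of the CBTI arms by an equal step: the pair differs by 0.61/2 = 0.31.
- Only PA-SMT differs: the pair differs by 0.

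**3. Power of the pair at ρ = 0.676.** The SD of a five-session mean is √(3.704/5) = 0.861. The direct test is a two-sided t test with 78 df and noncentrality (d/0.861) × √(40/2). For d = 0.53 this is 0.616 × 4.472 = 2.76, giving power 0.78. The conditional figures require the three-group F and the pairwise t both to be significant (200,000 simulated trials per pattern).

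| Pattern at f = 0.25 | Difference (SD) | Three-group test | Pair, direct | Pair, conditional |
|---|---|---|---|---|
| PA-SMT equals PA-CBTI | 0.53 | 0.81 | 0.78 | 0.73 |
| PA-SMT midway | 0.61 | 0.81 | 0.88 | 0.80 |
| PA-SMT outside by an equal step | 0.31 | 0.81 | 0.35 | 0.34 |
| Only PA-SMT differs | 0 | 0.81 | 0.05 | 0.05 |

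At ρ = 0.5 the first row becomes 0.86 direct and 0.83 conditional.

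**4. Fixed 0.5 SD partner effect, ρ = 0.676.** Direct power is 0.73. Conditional power is 0.67 if PA-SMT equals either CBTI arm and 0.61 if it is midway. It is 0.72 to 0.73 if PA-SMT lies well outside (0.3 SD above PA-CBTI or 0.5 SD below i-CBTI).

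**5. False positives for the pair with no partner effect.** The direct test gives 5%. The conditional test gives 2.5% when all arms are equal, rising to 5% as PA-SMT moves away.

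**6. Completion.** Randomised per arm: 120/0.8/3 = 50. Assumed rates are 85% versus 67%, the latter from the 33% dropout cited in the Background. Direct chi-squared power is 0.57. Conditional power is 0.51, 0.44 and 0.47 with PA-SMT at 85%, 76% and 67%. With PA-SMT at 95% it is 0.57, so the loss vanishes there too.

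**The case against.** A three-group test followed by pairwise comparisons is a recognised procedure. Two pairwise comparisons are planned, so some protection has a purpose. The article expects that "individuals under partner-assisted conditions will show greater adherence and lower attrition than those under the individual treatment condition" and says of PA-SMT, "We expect this condition to show high adherence without conferring benefits to sleep". In that pattern the loss is about 5 points. The larger losses need PA-SMT midway between the CBTI arms, which the article does not predict. The article attaches 0.81 openly to the MANOVA and does mention the follow-up comparisons. A condensed article may leave their detail to a fuller document.

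Most of this stands, and it rules out three stronger readings:
- A reader might infer that a group effect driven by PA-SMT would be reported as a partner effect. The plan does not allow this. The PA-CBTI versus i-CBTI comparison still decides, at no more than about 5% error.
- A reader might infer that the primary comparison is underpowered or that 0.81 is wrong. Neither can be shown. With ρ unstated, 0.81 can be neither confirmed nor refuted, and 0.78 to 0.86 for the expected pattern is compatible with adequate power.
- A reader might infer a steady loss of power. It is close to nil when PA-SMT lies well outside both CBTI arms, for adherence and for completion.

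The objection does not remove the mismatch. The article itself fixes the test order and the basis for the power figure, and neither follows the comparison it calls primary. Protection across several comparisons is no reason to make the one named in advance conditional.

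**Conclusion.** The point holds in a limited form. The stated primary comparison is conditional on a test that depends on a third arm, and the only power figure belongs to that test. The figure of 0.81 is compatible with power for the comparison anywhere from 0.05 to 0.88. In the expected pattern it is about 0.78 directly and 0.73 conditionally. For a 0.5 SD effect the loss ranges from almost nothing to 12 points (0.73 to 0.61).

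These sizes rest on an assumed correlation of about 0.68, assumed positions for PA-SMT, and a univariate simplification of the MANOVA. The mismatch between goal, test order and power figure rests on the text alone. The sequence is not invalid, but it costs power on the main question and offers no protection that a single pre-named comparison needs.

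**What to change.** In Statistical tests of hypotheses, Aim 1, make PA-CBTI versus i-CBTI the direct primary test of adherence over sessions 3–7, on the combined adherence outcome already planned, without requiring a significant group effect first. Do the same for completion under Hypothesis 1B. Keep PA-CBTI versus PA-SMT and the three-group tests as secondary analyses. The hypothesis wording on partner-assisted conditions can stay, since it agrees with Research aims and hypotheses.

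In Power considerations, state the power of the primary comparison with its assumed SD difference, 40 per arm and the between-session correlation. An example is about 0.78 for 0.53 SD at a correlation of 0.68.

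The cost is small. Arms, visits, sample size and data do not change if this is done before analysis. The stated power becomes slightly less favourable (0.78 rather than 0.81 in the expected pattern), and the three-group result becomes secondary.
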